#### Core Training

We will adapt Core Training as a blended strategy toolkit [39] wherein multiple interventions targeting multiple agency roles are combined to help sites increase FBS delivery. Core Training will convene administrators, supervisors, data managers, and clinical staff for two 3-h workshop sessions. *FBS System Mapping* will focus on process mapping of existing site policies and practices for engaging family members in treatment, with the goals of completing a needs assessment to identify addressable shortcomings in current FBS and identifying FBS performance indicators already captured in site records. Mapping information will be used to collaboratively select 2–3 data-based goals for FBS quality improvement that will become exemplars during the MTFS-I Installation session. *MTFS-I Installation* will consult on integrating MTFS-I procedures into existing site procedures and data systems. It will feature principles of data-driven decision-making whereby feedback reports on FBS performance levels can be used to address FBS improvement goals selected during system mapping. Per standard practice, sites receiving Core Training will be provided routine technical assistance [7] after training is completed.

#### Facilitation

We will provide facilitation procedures in the Core + Facilitation condition for 1 year after Core Training activities. Facilitation will reinforce Core Training instruction and foster sustainability of FBS improvements over time [38]. Facilitation will feature bi-weekly phone consultation with clinical staff during which MTFS-I components (mock videos, feedback reports) are reviewed and their applicability to active cases discussed. We will also convene quarterly on-site meetings with staff serving as a local change team [37] to review progress toward FBS improvements, discuss MTFS-I feedback reports and online resource use, and provide intensive technical assistance for progressing toward site-selected FBS improvement goals. Although the Facilitation strategy requires additional resource commitments, it is a commonly used strategy shown to be feasible and valuable for scaling behavioral innovations across a variety of behavioral care systems [7, 37].

### Study measures

The ITT-ABP collects post-session therapist-report data on family participation in treatment activities (clinical assessments, treatment planning meetings, therapy sessions) and therapist use of core family therapy techniques [19]: family engagement and goal setting, relational reframing, family skills building, and coaching family interactions. It requires 2–3 min to complete and has demonstrated construct validity [15], concordance with observational ratings [16], benchmark validity for community therapists [17], and predictive validity for multiple client outcomes [55]. Client outcome data will be extracted from a state-regulated management information system used to track all client episodes of care in licensed substance use treatment programs with regard to achievement of therapeutic goals and reduction of substance use. Baseline covariates will be assessed via three therapist-report measures. *Organizational Social Context* measure [56] yields scaled scores that can be compared to national norms describing the organizational context of behavioral health clinics with regard to Organizational Culture, Organizational Climate, and Work Attitudes [57]. *Evidence-Based Practice Attitude Scale* [58] is a 15-item measure of clinician attitudes regarding the appeal of EBIs, required use of EBIs, openness to trying EBIs, and unfavorable attitudes toward EBIs [58, 59]. *Therapist Self-Reported EBI Proficiency* [15] averages therapists’ own judgments about their degree of allegiance to, and their perceived technical skill in, multiple EBIs including family therapy.

### Study procedures

#### Observational evaluation of FBS delivery

For all consenting families treated by study therapists, we will collect session audio-recordings, a minimally intrusive procedure widely accepted by families and therapists in our previous studies [26] that has proven feasible in usual care for youth behavioral health [6, 27]. From among all collected recordings, we will randomly select one session from the early phase (sessions 1–3) and later phase (sessions 4+) of each case for coding with the observer version of the ITT-ABP [16]. We will use urn randomization to balance the coding sample on study condition and site factors (census, location). With 240 clients yielding on average 1.5 recordings apiece, we anticipate coding ~ 360 sessions, of which 20% will be double-coded to establish observer reliability. If observer fidelity verification reveals that some portion of study therapists exhibit unacceptably poor self-report reliability, the observational ratings can be used to calibrate or substitute for therapist-report ratings.

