### Training: upgrading therapist-report reliability by mimicking observational coding methods

Training clinicians to reliably self-report about treatment implementation is a pragmatic strategy to enhance fidelity monitoring and ultimately increase EBI delivery [6, 22]. Unfortunately, studies attempting to show concordance between therapist self-ratings and observer ratings of fidelity have mostly produced disappointing results, casting doubt on whether therapists can reliably rate their own performance [23]. This includes research-trained clinicians delivering manualized treatment [24, 25] as well as front-line clinicians in routine care [26, 27].

MTFS-I contains an innovative *Training* component with the goal of increasing the reliability of therapist-report fidelity tools such as the ITT-ABP. As detailed below, MTFS-I utilizes online training methods to coach community clinicians to be fluent in fidelity self-rating by employing procedures analogous to those used to train observational fidelity raters in controlled studies [28]. Gold-standard observational methods, used primarily in research settings to confirm the integrity of experimental treatments, require numerous hours for introducing the coding scheme, reviewing recordings to calibrate scoring, and convening meetings throughout coding activities to prevent coder drift [28]. Directly transporting these methods to everyday care—that is, training agency staff on site to reliably assess treatment delivery by their supervisees or colleagues—is beyond the normal resource capacity of most providers. However, some have asserted that by mimicking observational methods, it may be possible to improve the reliability (and hence, utility) of therapist self-reports [6, 23, 27]. The approach most likely to succeed is online training, wherein reporter training content can be presented in a pragmatic, user-tailored manner [29]. MTFS-I online training procedures for therapist self-reporting on FBS delivery are described in the “Methods/design” section.

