MTFS-I training components are delivered weekly to therapists and supervisors. *ITT-ABP reporter training modules*: MTFS-I contains brief illustrative descriptions and related clinical exemplars describing family therapy scale items from the ITT-ABP. Each module covers 2–3 items and will conclude with learning quizzes with corrected scoring feedback. Reporter training also includes elements aimed at reducing self-report biases of various kinds, by providing continuous training in unbiased, accurate reporting [48]. *Mock FBS session coding*: 5–8 min video segments are used to model examples of ITT-ABP items, illustrating a range from moderate to high fidelity in order to support differentiated scoring. The staff will be asked to code segments directly after completing the corresponding reporter training module for those items in order to reinforce training elements. The staff will submit ITT-ABP ratings for the segment and immediately view gold standard scores, along with an explanation justifying the gold standard scoring. As discussed above, these procedures mimic well-established observational training methods and leverage immediate corrective feedback on objectively rated samples of desired performance [34]. In addition to supporting self-report reliability, these methods have strong potential for increasing FBS use via observational learning mechanisms prompted by modeling of quality FBS delivery depicted in the segments [49]. Although live coaching and guided skills practice are the most effective means to acquire new clinical skills [45], video-based modeling has shown promise for increasing use of EBIs of several kinds (e.g., [50, 51]).

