#### FBS fidelity, MTFS-I uptake, and outcome data collection

ITT-ABP checklists and session recordings will be collected at all sites during the Baseline and Implementation phases. During the Implementation Phase, therapists and supervisors will be asked to confirm review of monthly MTFS-I feedback reports (distributed via email) and complete online reporter training modules and mock FBS session coding; also, therapists will report on the extent to which mock segments and feedback reports are discussed during routine clinical and peer supervision. To collect outcome data, we will use existing arrangements with the state regulatory agency for extracting archived data for all admissions of clients age 13–21 for 1 year prior to initiating Core Training activities (Baseline) and 1 year after (follow-up).

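### Therapist-scored technique use can move because reporting changes, and the planned checks would not show this by phase or arm

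*Protocol article*

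**What the plan says.** The outcome is self-scored. Under Study measures, "The ITT-ABP collects post-session therapist-report data on family participation in treatment activities" and on the therapist's use of core family therapy techniques. The aim 2 fidelity power calculation is built on these therapist reports.

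The intervention acts on the scoring. The Background section on training describes a component "with the goal of increasing the reliability of therapist-report fidelity tools such as the ITT-ABP". The section on MTFS-I online training components adds: "Reporter training also includes elements aimed at reducing self-report biases of various kinds".

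The timing differs by phase. The data collection section says "ITT-ABP checklists and session recordings will be collected at all sites during the Baseline and Implementation phases", but the modules, mock-session coding and feedback belong to the later period: "During the Implementation Phase, therapists and supervisors will be asked to confirm review of monthly MTFS-I feedback reports", and to complete the online training.

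Exposure can differ by arm. Both arms receive MTFS-I. Facilitation adds "bi-weekly phone consultation with clinical staff during which MTFS-I components (mock videos, feedback reports) are reviewed", and the Specific aims hypothesise higher uptake of the online training in Core + Facilitation.

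On observation, the Abstract bases FBS delivery on both therapist-report and observational data, and about 360 recorded sessions are to be coded. If that checking finds that "some portion of study therapists exhibit unacceptably poor self-report reliability, the observational ratings can be used to calibrate or substitute" for therapist ratings, the self-reported outcome may be altered. The Data analysis plan gives a therapist-observer intraclass correlation with no division by phase or arm. It does not state a Phase or Condition test on observer scores.

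**The concern.** Baseline checklists come from therapists not yet trained by MTFS-I in scoring, and Implementation checklists from therapists who are being trained. If training changes how the same session is scored, the mean moves although delivery has not. Bias-reduction training could lower scores and hide a real gain. Feedback plotted against site benchmarks could raise them and imitate one.

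A shift common to both arms goes wholly into the aim 1 Phase contrast and cancels in the Condition contrast. A shift that differs by arm goes into aim 2, and the hypothesised uptake difference makes that plausible.

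A single pooled agreement coefficient blends mean difference with scatter. It shows neither the direction of a shift nor whether it changed between phases or arms. A rule that is invoked once poor reliability has been seen, and that permits substitution, could make one outcome out of two kinds of rater.

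The point concerns technique use. MTFS-I uptake is not a technique score and is not affected in this way.

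**Working it through.** **Inputs from the protocol.** 5 sites per arm; 6 active therapist slots and 48 clients per site; about 6 sessions per case, hence 288 checklists per site; intraclass correlation 0.05 at each of the two upper levels, read here as site and therapist; SD 0.63; meaningful change 0.45 × 0.63 = 0.28 points. About 240 clients (24 per site) with 1.5 coded sessions each give 360 codings, which is 12.5% of 2880 checklists.

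**Assumed.** Two-sided alpha 0.05; total variance 1.

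**The plan's own figure.** Variance of a site mean = 0.05 + 0.05/6 + 0.90/n; SE of the arm difference = √(2 × variance/5).
- n = 288 checklists: variance 0.0615, SE 0.157, power at 0.50 = 0.797 (t, 8 df).
- n = 48 clients: variance 0.0771, SE 0.176, power 0.813 (normal) or 0.70 (t, 8 df).

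The stated power of about 0.80 reproduces.

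**Effect of a differential reporting shift on aim 2, with delivery unchanged.** Shift in SD units = points/0.63, divided by SE 0.176 (48 clients per site). The shift sizes are assumptions. The last two columns give the chance of a significant result in the direction of the shift.

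| Shift (points) | SD units | Normal | t, 8 df |
|---|---|---|---|
| 0.10 | 0.159 | 0.15 | 0.12 |
| 0.20 | 0.317 | 0.44 | 0.36 |
| 0.28 | 0.450 | 0.73 | 0.61 |

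**Precision of an observer-based result, between arms.** Let c be the client share of variance (assumed 0.2 to 0.4) and 0.9 − c the session share. Self-report variance = 0.0583 + c/48 + (0.9 − c)/288. Observer variance = 0.0583 + c/24 + (0.9 − c)/36.
- c = 0.2: 0.0649 and 0.0861; SE 0.161 and 0.186; ratio 1.15.
- c = 0.4: 0.0684 and 0.0889; SE 0.165 and 0.189; ratio 1.14.

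**Precision for the within-site Phase contrast.** Stable site and therapist effects are taken to cancel. Cases are assumed to split 4:12 by months, so 12 Baseline and 36 Implementation clients per site, and half of each when recorded. Let s be an assumed site-by-phase variance, entering once per phase.
- Self-report: c(1/12 + 1/36) + (0.9 − c)(1/72 + 1/216) + 2s.
- Observer: c(1/6 + 1/18) + (0.9 − c)(1/9 + 1/27) + 2s.

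| c | s | Self-report | Observer | SE ratio |
|---|---|---|---|---|
| 0.2 | 0 | 0.0352 | 0.1481 | 2.05 |
| 0.4 | 0 | 0.0537 | 0.1630 | 1.74 |
| 0.2 | 0.005 | 0.0452 | 0.1581 | 1.87 |
| 0.4 | 0.025 | 0.1037 | 0.2130 | 1.43 |

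If the 48 cases are instead the Implementation year alone, with 16 more at Baseline, the last row becomes 0.0903 and 0.1722, ratio 1.38. The range is roughly 1.4 to 2.1.

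**The case against.** The strongest reply is that observation is already built in. The Abstract names it as a basis for comparing FBS delivery, the sample size section refers to observational fidelity analyses, recordings are made in both phases, sessions are coded whatever the therapist's reliability, and the Discussion says observation verifies self-report. This stands: a reader might infer that the calibrate-or-substitute clause is the only safeguard, and the protocol does not support that. What remains is that the analysis text does not state how the observer scores enter the Phase and Condition contrasts, and that the one rule it does give is triggered by results.

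Other stronger readings also fail:
- **Substitution only for poor reporters.** The wording about some therapists describes the trigger. It does not clearly limit the consequence, and calibration is offered as well. Mixed rating sources are a possibility under the rule, not a certainty.
- **The 2.4 versus 2.0 gap as over-reporting.** The Power analysis presents the community and research means as a fidelity difference. Nothing there attributes it to reporting, so it cannot size the bias.
- **Observer scores as a cheap primary outcome.** The 15% loss applies only between arms; the Phase contrast loses much more, and the result would rest on consenting families. That choice is debatable.
- **A coded sample unbalanced on Phase.** Study phase is not among the urn factors, but an early and a later session are sought from each case, so phase representation follows case flow.

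It is also fair that aim 1 is labelled exploratory and that both arms receive the same online training, so only a differential shift biases aim 2.

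**Conclusion.** The point holds for therapist-reported technique use. As written, a change in reporting could be read as a change in delivery: directly in the exploratory aim 1 contrast, and in aim 2 to the extent that the shift differs by arm. The direction cannot be predicted from the protocol.

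The protocol gives no figure for the size of any shift. The probabilities above therefore show sensitivity and are not estimates of bias: a differential shift of 0.20 points, below the 0.28 counted as meaningful, would give a significant arm difference in 36 to 44% of trials with no difference in delivery. They rest on two-sided alpha 0.05, the protocol's intraclass correlations and a between-arm comparison of site means. The material needed to detect such a shift is already to be collected; the analysis text does not yet use it for that purpose.

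**What to change.** 1. Report the mean therapist-minus-observer difference, and the reliability coefficient, by Phase and Condition.
2. Replace the results-triggered rule with one prespecified calibration model, observer score on therapist score with Phase, Condition and their product, applied to all therapists. Do not substitute observer scores for a subset of therapists.
3. Prespecify the Phase and Condition contrasts on the roughly 360 observer-coded sessions as a supporting analysis beside self-report.

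This needs changes to analysis wording only, using recordings and codings already planned. The price is in interpretation. The observer-based result covers only consenting, recorded families and has the wider standard errors derived above, so it should be read as support for, or a warning about, the self-report result. The calibration model rests on the same recorded sessions and carries the same limit on coverage.

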#### Multireporter evaluation of implementation strategies

To verify the fidelity of the implementation strategies, Core Training and Facilitation, we will employ the JJ-TRIALS fidelity toolkit [38, 39] to evaluate implementation adherence and differentiation throughout the study. Toolkit materials include trainer- and participant-report tools assessing intervention preparation, workshop delivery of goal selection and data-driven decision-making content, knowledge and skills gained during core training, and perceived facilitation effectiveness.

#### FBS fidelity, MTFS-I uptake, and outcome data collection

ITT-ABP checklists and session recordings will be collected at all sites during the Baseline and Implementation phases. During the Implementation Phase, therapists and supervisors will be asked to confirm review of monthly MTFS-I feedback reports (distributed via email) and complete online reporter training modules and mock FBS session coding; also, therapists will report on the extent to which mock segments and feedback reports are discussed during routine clinical and peer supervision. To collect outcome data, we will use existing arrangements with the state regulatory agency for extracting archived data for all admissions of clients age 13–21 for 1 year prior to initiating Core Training activities (Baseline) and 1 year after (follow-up).

### Power analysis

With cluster trials, power is substantially affected by the number of sites and clusters (i.e., therapists) within site, and minimally by clients within cluster [42]. For aim 2 (therapist-report fidelity data), in which the unit of analysis is ITT-ABP checklists (*n* = 2880), using an effect size of 0.50 for paired contrasts between conditions, with 5 sites per comparison and 48 clients within each site, and with moderately sized intraclass correlations at levels 2 and 3 (*ρ* = 0.05) [60], yielded power of approximately 0.80*.* Our recent fidelity study [17] found the mean Family Therapy fidelity score for community therapists (2.4; SD = 0.63) was significantly higher than that for research therapists (2.0/.35). Using the standard deviation of Family Therapy fidelity scores produced by community therapists (a sample similar to the current study) and an effect size of 0.45 yields a product of 0.28, a threshold indicating meaningful change in fidelity (as illustrated by the difference found between community versus research therapist scores) that would yield a significant effect with power = 0.80. For aim 3 (archived outcome data), in which the unit of analysis is the client, for 1200 clients and assuming 10 sites and 80 therapists, an effect size of *δ* = 0.50 in line with that found similar implementation studies (e.g., [61]) yielded power = 0.80.

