### Data analysis plan

Study data will have a three-level nested structure: clients within therapists, within sites (we will average across sessions for each client). The analytic approach for these nested data will be multilevel mixed-effects models examining the effects of Condition and Phase on dependent variables aggregated across each time period: 4-month Baseline phase (prior to Core Training) and 12-month Implementation phase. We will use maximum likelihood estimation for continuous variables and robust weighted least squares for categorical variables. We will model Site and Therapist as random effects in all models. We will include Site (census, location, organizational context), Therapist (age, sex, ethnicity, experience, EBI attitudes, family therapy proficiency), and Client (age, sex, race/ethnicity, family composition) factors at their respective levels to examine potential covariance effects. Variables representing adherence to Core Training and adherence to Facilitation will be entered at the Site level to ensure that fidelity differences do not confound experimental comparisons; these factors will also be tested as potential moderator variables. Effect sizes will be calculated using the standardized *d* effect size indicator, interpreted as the standardized difference between contrasts: between Conditions (Core Training vs. Core + Facilitation) and Phase (Baseline vs. Implementation) [42].

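### The aim 2 power text claims about 0.80 at both d = 0.50 and d = 0.45 on one stated design, and its unit (checklists) differs from the unit of the analysis plan (client averages)

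*Protocol article*

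**What the plan says.** The Power analysis section describes aim 2 as a comparison "in which the unit of analysis is ITT-ABP checklists", with n = 2880. Its first calculation proceeds by "using an effect size of 0.50 for paired contrasts between conditions, with 5 sites per comparison and 48 clients within each site", "with moderately sized intraclass correlations at levels 2 and 3" (0.05), and it "yielded power of approximately 0.80".

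The same paragraph then takes from an earlier fidelity study the "mean Family Therapy fidelity score for community therapists (2.4; SD = 0.63"), against 2.0 (SD 0.35) for research therapists. It continues that "an effect size of 0.45 yields a product of 0.28, a threshold indicating meaningful change in fidelity", and states power of 0.80 for that difference. No other number of sites, ICC, alpha or test is given for this second claim.

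The Data analysis plan describes the data as "clients within therapists, within sites (we will average across sessions for each client"), with site and therapist as random effects. The section on sites and sample size supplies the counts: ten sites, six active therapist slots per site, eight cases per slot per year (480 cases) and about six sessions per case (2880 checklists).

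**The concern.** Power rises with the effect size, so one design with one test cannot have the same power at 0.50 and at 0.45. At least one of the two figures is therefore wrong, or the two rest on different calculations that the article does not separate.

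The difference in unit makes this harder to resolve. An ICC of 0.05, an SD of 0.63 and a standardized effect mean different things for single checklists and for client averages, and the article does not say which it means.

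Aim 2 is the randomized comparison of the two implementation strategies on delivery of family-based services. A reader will take 0.28 points as a difference that the trial would detect four times in five. If the power at that difference is lower, a non-significant aim 2 result carries less information than the article implies.

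**Working it through.** **Inputs.** From the article: 5 sites per arm; 6 therapists per site; 8 clients per therapist (48 per site); 6 sessions per client (288 checklists per site); ICC 0.05 at each of two levels, read here as therapist and site; SD 0.63. Assumed, because not stated for aim 2: two-sided alpha 0.05.

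**Formulas, in SD units.** Variance of a site mean = ρ_site + ρ_therapist/6 + (1 − ρ_site − ρ_therapist)/n, where n is the number of units per site. SE of the difference between arms = √(2 × that variance / 5). Power comes from d/SE, by normal approximation or by noncentral t. The t version has 8 df for ten sites in two arms, or 4 df if the analysis is done on five pairs.

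**Step 1: the plan's first figure, client averages (n = 48).**
Site-mean variance = 0.05 + 0.05/6 + 0.90/48 = 0.05 + 0.00833 + 0.01875 = 0.0771.
SE = √(2 × 0.0771/5) = 0.1756.
At d = 0.50, d/SE = 2.85 and normal-approximation power is 0.81. The stated value of about 0.80 is reproduced.

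**Step 2: the second figure by the same calculation.**
At d = 0.45, d/SE = 2.56 and power is 0.73, not 0.80.

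**Step 3: other readings, two-sided.**

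| Unit and test | d = 0.50 | d = 0.45 |
|---|---|---|
| Client averages, normal | 0.81 | 0.73 |
| Client averages, t with 8 df | 0.70 | 0.61 |
| Client averages, t with 4 df, no gain from matching | 0.58 | 0.50 |
| Checklists treated as independent within therapist (n = 288), normal | 0.89 | 0.82 |
| Same, t with 8 df | 0.80 | 0.71 |
| Session-level ICCs, client variance share 0.1, normal | 0.88 | 0.81 |
| Session-level ICCs, client variance share 0.2, normal | 0.87 | 0.80 |

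For the checklist rows, site-mean variance = 0.05 + 0.00833 + 0.90/288 = 0.0615 and SE = 0.1568. For the last two rows, with client share c, the final term becomes c/48 + (0.90 − c)/288. No row has 0.80 in both columns.

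**Step 4: a check that needs no ICC, unit or cluster size.** Choose the SE so that power is exactly 0.80 at d = 0.50. Power at 0.45 is then 0.71 (normal), 0.71 (8 df) or 0.72 (4 df). Conversely, 0.80 at 0.45 implies 0.87 to 0.88 at 0.50.

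**Step 5: effect detectable with power 0.80, client averages.** Normal: d = 0.49, and 0.492 × 0.63 = 0.31 points. With 8 df: d = 0.56, and 0.562 × 0.63 = 0.35 points. With 4 df and no matching gain: d = 0.66, and 0.660 × 0.63 = 0.42 points.

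**Step 6: the threshold.** 0.45 × 0.63 = 0.2835, so the product of 0.28 is right. The community-versus-research difference offered as illustration is 2.4 − 2.0 = 0.40 points.

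**The case against.** Several stronger readings are tempting, and the document does not support them.

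- **That the 0.50 figure is wrong.** It reproduces at 0.81 on client averages by normal approximation. With 8 df it is about 0.80 on independent checklists, and still 0.79 or 0.78 when sessions are clustered within clients at a variance share of 0.1 or 0.2, so independence of checklists is not required. The value of 0.70 rests on client averages and 8 df. The article names maximum likelihood mixed models, and the df method may properly be left to an analysis plan that is not shown.
- **That 0.45 fails on every reading.** With session-level ICCs and a normal test it reaches about 0.80 to 0.82. A one-sided normal test on client averages also gives 0.82. In each case power at 0.50 becomes about 0.87 to 0.89, so the pair of claims still fails.
- **That averaging sessions itself loses power.** In balanced data it does not. The unit matters because it fixes what the ICC, SD and d describe.
- **That the 0.40-point gap contradicts 0.28.** The article calls 0.28 a threshold and offers the gap as an illustration. An observed 0.40 exceeds 0.28, so this is a loose anchor and not a contradiction.
- **That 0.28 should be replaced by 0.35.** A meaningful-change threshold should not move to match what a trial can detect.

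It is also fair that yoked pairs, the baseline phase and covariates could raise power. With 8 df, explaining about half of the site and therapist variance would bring d = 0.45 to 0.81. With 4 df, pairing that removed 75% of site variance would give 0.76, and 90% would give 0.84. The article quantifies no such gain.

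**Conclusion.** The point holds in two parts. First, the two claims of 0.80, at 0.50 and at 0.45, cannot both be true of the one design described. The gap is about 8 to 9 percentage points if the figure at 0.50 is right, and about 7 to 8 if the figure at 0.45 is. This needs no assumption about ICC, unit or df, and the word approximately does not cover it. Second, the unit in the Power analysis section conflicts with the unit in the Data analysis plan.

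The size of any shortfall at 0.28 points is less certain. On client averages with the stated ICCs, power there is 0.73 by normal approximation and 0.61 with 8 df. The chance of missing such a difference is then 27% to 39%, not 20%. These figures assume two-sided alpha of 0.05, take the ICCs at client level, and credit nothing to matching, baseline or covariates. A reader might infer that the trial is firmly underpowered for 0.28 points; the article does not settle that either way. What is established is that its power statement is inconsistent and that, on the unit of its own analysis plan, the 0.80 claim at 0.45 is not reproduced at two-sided 0.05 without such a gain.

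**What to change.** Rewrite the aim 2 part of the Power analysis section so that it:

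- names one unit, the client average, to match the Data analysis plan;
- says at which level the ICC of 0.05 and the SD of 0.63 are defined;
- states alpha, sidedness, and the test or df, including whether the analysis respects the yoked pairs;
- gives one power per effect size (with 8 df, about 0.70 at d = 0.50 and 0.61 at d = 0.45);
- reports the effect detectable with 80% power: about d = 0.56 (0.35 points) with 8 df, or d = 0.49 (0.31 points) by normal approximation;
- states and quantifies any gain assumed from pairing, baseline or covariates.

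Remove the claim of 0.80 power for 0.28 points. Keep 0.28 as the meaningful-change threshold if it has its own justification, and note that the difference cited to illustrate it is 0.40 points.

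The cost is wording only. A stated figure becomes less favourable, and no sites, therapists or clients are added.
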